### Secondary endpoints

***Survival until 10 weeks after randomization.*** International treatment guidelines recommend 10 weeks of high dose antifungal therapy for cryptococcal meningitis – an initial phase of amphotericin based induction therapy for 2 weeks followed by 8 weeks of moderate to high dose fluconazole. The rate of survival until this 10 week period of therapy is completed is a frequent endpoint in trials of treatment for cryptococcal meningitis
^8,
9,
44^. Improvements in EFA over the first 2 weeks of treatment have been associated with improved survival at 10 weeks. Therefore survival until 10 weeks after randomization will be a secondary endpoint in this study.

***Disability at 10 weeks.*** Disability is an expected consequence of cryptococcal meningitis, including blindness, deafness and other focal neurological deficits. In addition to improving the sterilizing power of antifungal therapy, Tamoxifen may also reduce the rates of disability in survivors. Neurological disability will be assessed using the modified Rankin score and the Two Simple Questions and classified as good, intermediate, severe disability, or death, as previously described
^45^.

***Adverse events.*** The proportion of patients with any grade 3 or 4 adverse event, serious adverse event, or unexpected serious adverse event will be compared between treatment groups.

***Rate of IRIS until 10 weeks (in HIV infected patients only).*** We will model the rate of IRIS over time with a cause-specific hazards model taking into account the competing risk of prior death. CM-related IRIS will be defined as per the recent proposed definition
^46^.

***Rate of Cryptococcal meningitis relapse.*** A pragmatic definition of relapse will be used. This is defined as either intensification of antifungal therapy above that according to the study antifungal schedule, or readmission for treatment of cryptococcal disease.

***QT prolongation.*** Prolongation of the QT interval is a potential side-effect of both Tamoxifen and fluconazole, although it is not clear that either drug increases the risk of Torsade de Pointes, a potentially life-threatening arrhythmia. The QT interval will be estimated manually from 3 chest and 3 limb leads from a high resolution (50mm/sec) 12-lead ECG. The median value will be determined and used to calculate the corrected QT interval (QTc) using Framinghams’ formula.

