### Disability at 10 weeks.

The disability score at week 10 follow-up is defined as the higher (worse) of “ the two simple questions” and the Rankin score assessed at that time point, and will be categorized as good outcome, intermediate disability, severe disability, or death (in case the patient died before 10 weeks) as previously described
^45^. The ordinal 10-week score (“good”>”intermediate”>”severe”>”death”) will be compared between the two arms with a proportional odds logistic regression model depending on the treatment arm and HIV infection status. The result will be summarized as a cumulative odds ratio with corresponding 95% confidence interval and p‐value. Patients lost to follow up will be analyzed according to their last recorded disability status. If the rate of patients lost to follow-up exceeds 10%, we will also perform an alternative analysis based on multiple imputation of missing values.

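### 10-week disability: carry-forward of the last recorded status is the main handling of losses, no earlier score is named, and the planned multiple imputation runs only above 10% loss

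*Protocol article*

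**What the plan says.** The analysis section on disability at 10 weeks in the protocol article fixes four things.

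- **The score.** The endpoint takes the worse result on two instruments at the week-10 visit; for the second of them the text reads "the Rankin score assessed at that time point". It has four ordered categories: good, intermediate, severe and death. Death applies "in case the patient died before 10 weeks".
- **The model.** A "proportional odds logistic regression model depending on the treatment arm and HIV infection status", reported as a cumulative odds ratio with a 95% confidence interval and p-value.
- **Losses, main handling.** "Patients lost to follow up will be analyzed according to their last recorded disability status".
- **Losses, further handling.** "If the rate of patients lost to follow-up exceeds 10%, we will also perform an alternative analysis based on multiple imputation of missing values".

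The Secondary endpoints section names the same two instruments ("Neurological disability will be assessed using the modified Rankin score and the Two Simple Questions") under a heading that refers to 10 weeks only. Table 2 has a Clinical Assessment row on days 1, 3, 7, 11, 14, 21, 28, 42 and 70 but does not list what it contains, and it has no row for either instrument. The Clinical monitoring section lists visits weekly to week 4, then at weeks 6 and 10, and mentions no disability score at any of them.

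**The concern.** The outcome is a state at week 10. The main analysis fills a missing week-10 state with an earlier one, and the article does not say where the earlier one comes from. Two cases are possible, and the rule has a problem in each.

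1. **No score is taken before week 10.** A patient lost earlier then has nothing to carry forward, and the rule gives no result.
2. **Scores are taken earlier.** The last one may date from the acute illness or early recovery. All patients spend the first 14 days in hospital on amphotericin, and both recovery and death are expected between then and week 10. A patient who recovers after loss keeps the worse score. A patient who dies after loss, without the trial learning of it, is analysed as a survivor. A single filled-in value is also treated as if it had been observed, so the confidence interval is too narrow for what is known.

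The trial is open-label, so losses could differ between arms, and carry-forward error would then enter the treatment comparison. The article neither shows nor predicts such a difference. The method that would carry the uncertainty, multiple imputation, is already in the plan, but only as an additional analysis and only above a threshold.

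**Working it through.** **Plan's own figure.** The article gives no power, effect size or expected loss rate for the disability outcome, so there is no stated figure to reproduce. Its power statement concerns early fungicidal activity only.

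**Step 1: how many patients the threshold leaves to carry-forward alone.** Inputs: 50 patients (25 per arm), and imputation only if loss exceeds 10%.

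- 5/50 = 10%, which does not exceed 10%, so there is no imputation.
- 6/50 = 12%, which does, so imputation is added.

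Up to 5 patients can therefore rest on carry-forward alone. Above 5, carry-forward still remains the main analysis.

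**Step 2: how far a few carried values can move the estimate.** The article gives no outcome distribution by category, so the counts are an assumption: 8 good, 5 intermediate, 4 severe and 8 dead in each arm of 25. The 8 deaths (8/25 = 32%) sit between the 31% and 33% 10-week mortality that the Background reports for the two combination arms of the earlier Vietnamese trial. The split of the survivors is arbitrary.

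Model: logit P(Y > k) = −α_k + β × arm, with the categories ordered from good to death. The odds ratio is exp(β), and above 1 means worse in the affected arm. HIV status is left out because its joint distribution with outcome is unknown. One arm stays at 8/5/4/8. In the other, m truly good patients are carried as severe, giving (8 − m)/5/(4 + m)/8.

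| m | Counts in the affected arm | Odds ratio | 95% CI |
|---|---|---|---|
| 0 | 8/5/4/8 | 1.00 | 0.37 to 2.72 |
| 1 | 7/5/5/8 | 1.12 | 0.41 to 3.04 |
| 2 | 6/5/6/8 | 1.26 | 0.46 to 3.41 |
| 3 | 5/5/7/8 | 1.41 | 0.52 to 3.83 (p about 0.50) |

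**Step 3: the opposite error.** If 1, 2 or 3 patients in one arm died unrecorded and are carried as severe (8/5/(4 + m)/(8 − m)), the odds ratio is 0.94, 0.88 or 0.83. The direction of any bias is therefore not fixed.

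**Step 4: losses in both arms.** One good patient carried as severe in each arm gives 1.00. Three in one arm against two in the other gives 1.12. The error largely cancels when losses are balanced.

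**Step 5: the full 5 losses in one arm.** Take 20 observed patients in that arm (6/4/3/7) plus 5 lost, against 8/5/4/8.

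| State given to the 5 lost patients | Odds ratio | 95% CI |
|---|---|---|
| Carried as severe | 1.24 | 0.46 to 3.36 |
| Truly good | 0.69 | 0.25 to 1.91 |
| Truly intermediate | 0.98 | 0.36 to 2.66 |
| Truly dead | 1.72 | 0.62 to 4.75 |

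Carry-forward reports one of these rows as if it were known. The true state could give any of the others. Every interval in this working includes 1.

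**The case against.** **A reader might infer that disability is scored only at week 10.** The documents do not support that. The phrase "the Rankin score assessed at that time point" defines which scores form the endpoint; it does not say that none are taken earlier. Table 2 has no disability row even on day 70, when the score is certainly taken, so its silence about other days proves nothing. The Clinical Assessment row is not itemised, a rule about a last recorded status presupposes earlier records, and the full protocol behind this condensed article is not shown. What stands is narrower: the article names no earlier score.

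**A reader might infer that the rule counts all lost patients as alive.** It does not. Known deaths before week 10 have their own category, and the Clinical monitoring section has date and cause of death recorded. Only deaths that nobody learns of are affected. Imputation would not observe those either; it would have to model them.

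**A reader might infer that the outcome is distorted.** That is not shown. The largest shifts above need every loss to fall in one arm and every carried score to be wrong by two categories. The article gives no loss rate and no reason to expect imbalance, and follow-up lasts only 10 weeks. Even three such errors move the estimate far less than the width of its interval.

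**The two complaints exclude each other.** If no earlier score exists, nothing is carried and nothing is biased; if scores exist, the rule works. That is correct, and they are put here as alternatives. The rule is weak under each, for a different reason.

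**The remedy is partly preference, and the stakes are limited.** The plan does fix a rule, a trigger and an imputation analysis in advance. The endpoint is secondary in a 50-patient phase II trial whose primary endpoint is early fungicidal activity. This limits how serious the point is. It does not make carry-forward the better main analysis.

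**Conclusion.** The point holds in a limited form. The article fixes single carry-forward as the main handling of a week-10 ordinal outcome, does not name the assessment that supplies the carried value, and holds back the better method it already plans unless loss exceeds 10%. Up to 5 of 50 patients could be analysed on carry-forward alone.

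The rule can bias the cumulative odds ratio in either direction: up to 1.12, 1.26 or 1.41 for one to three good patients carried as severe, and down to 0.94, 0.88 or 0.83 for one to three unrecorded deaths carried as severe. These figures rest on assumed counts of 8/5/4/8 per arm, errors in one arm only, and a model without HIV status. They show sensitivity and do not predict a bias. With an interval of about 0.37 to 2.72 before any error, no conclusion is shown to change.

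**What to change.** 1. Make the multiple imputation already planned the main handling at any level of loss, and drop the 10% trigger. Use arm, HIV status, baseline Glasgow coma score, and any earlier disability score or the last recorded Glasgow coma score as predictors. Where vital status is unknown, let the imputation run over all four categories, death included.
2. Keep known deaths before week 10 in the death category, as now.
3. Report carry-forward as a sensitivity analysis, restricted to patients who have an earlier score, and name the visits at which both instruments are scored.

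**Cost.** Both analyses are already foreseen, so the change is mainly one of order, with slightly more analysis work. Imputation brings a missing-at-random assumption, which must be stated, and with few losses in 50 patients the predictor set must stay small. The Trial status section says that enrolment has finished and analysis is under way, so the change should be dated and both results shown.

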### Adverse events.

The frequency of serious and grade 3 & 4 adverse reactions as well as the frequency of specific adverse events will be summarized (both in terms of the total number of events as well as the number of patients with at least one event). The proportion of patients with at least one such event (overall and for each specific event separately) will be summarized and (informally) compared between the two treatment groups based on Fisher’s exact test.

### QT prolongation

The QTc will be classified as “normal” (<450ms for males, <460ms for females), mildly prolonged (≥450ms for males or ≥460 for females but ≤500ms) and prolonged (>500ms). The frequency of patients with a maximum QTc in these categories will be summarized for the following time intervals: day 1 (baseline), days 2-3, 4-7, 8-14, and after day 14. Comparisons will be with a proportional odds logistic regression model depending on the treatment arm and HIV infection status.

The maximum absolute change from baseline of the QTc during follow-up will also be summarized; the comparison between treatment groups will be based on a linear regression model with treatment as the main covariate and adjustment for HIV status and the baseline QTc interval.

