### Cardiac monitoring

ECGs (50mm/sec) will be performed twice daily immediately before and 2 hours after administration of Tamoxifen during the first 14 days, and on days 21 and 28. ECGs can be repeated more frequently according to the patient’s needs. The QTc will be calculated as described in section ’Prolongation of the QT Interval’.

*Laboratory monitoring*

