## Blood

Inpatient laboratory monitoring will be as shown in the study schedule (
Table 2). Patients will have daily monitoring of potassium and alternate day monitoring of creatinine, calcium and magnesium levels for the first 2 weeks of the study(i.e. days 1, 3, 5, 7, 9, 11, and 14. Following this point levels will be monitored as clinically indicated. Full blood count will be measured at study entry, and at days 7 and 14, and thereafter as clinically indicated. CD4 count will be measured in all patients during week 1 and at day 70.

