### Analysis of other secondary outcomes

The rate of IRIS and the rate of relapse (defined as antifungal treatment intensification or re-treatment) will be modeled with cause-specific proportional hazards models with treatment as the only covariate and stratification by HIV infection status.

The visual acuity at 10 weeks is recorded on a 6 point scale and will be summarized by treatment arm for each eye separately, and overall where “overall” is defined as the worst recorded acuity of either eye. The odds of having “normal acuity” (amongst all surviving patients with a visual assessment) will be informally compared between the treatment arms with a logistic regression model adjusted for HIV status.

The time to the first new neurological event or death until 10 weeks will be analyzed in the same way as overall survival. Longitudinal measurements of intracranial pressure during the first 2 weeks will be modeled using a mixed effect model as described for the primary outcome. CD4 cell count at baseline and 10 weeks will be summarized and the change compared between the two groups based on a linear regression model with treatment as the main covariate and adjustment for HIV status and baseline CD4 cell count.

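### The QTc interval table counts all of day 1 as baseline, although day 1 includes an ECG taken 2 hours after the first tamoxifen dose

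*Protocol article*

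**What the plan says.** The Protocol article, section QT prolongation under the analysis of secondary endpoints, gives two analyses.

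- A categorical table (normal, mildly prolonged, prolonged above 500 ms): "The frequency of patients with a maximum QTc in these categories will be summarized", with the intervals given as "summarized for the following time intervals: day 1 (baseline), days 2-3, 4-7, 8-14, and after day 14". The test follows: "Comparisons will be with a proportional odds logistic regression model depending on the treatment arm and HIV infection status". No interval is exempted from it.
- A change analysis: "The maximum absolute change from baseline of the QTc during follow-up will also be summarized". Arms are compared by linear regression with "adjustment for HIV status and the baseline QTc interval". The section does not say which ECG supplies that baseline.

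The Cardiac monitoring section has ECGs "performed twice daily immediately before and 2 hours after administration of Tamoxifen during the first 14 days, and on days 21 and 28". The Prolonged QTc section repeats the pre-dose and 2-hour post-dose timing. Table 2 shows two ECGs a day for the first 14 days, and its footnote starts study drug on day 1. The section on prolongation of the QT interval applies twice-daily ECGs to all patients, controls included.

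**The concern.** Placed next to the ECG schedule, the label on the first interval is wrong. Day 1 is a treatment day and one of its two scheduled ECGs follows the first dose. Because each interval is summarised by its maximum, the post-dose value defines the day-1 category whenever it is the higher of the two. On-treatment intervals begin on day 2, so the first treated reading belongs to none of them.

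The abstract names QT prolongation as a side effect of particular interest, the Prolonged QTc section expects it in roughly 10% to 50% of patients, and the results are meant to inform whether a larger trial goes ahead. If tamoxifen prolongs QTc soon after the first dose, the error works in one direction: part of the harm is relabelled as a pre-existing state. A reader who saw more prolonged values in the tamoxifen arm's day-1 row would naturally take it for chance imbalance at entry.

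**Working it through.** The protocol states no figure for this endpoint, so there is none to reproduce. The check has a textual part and an illustrative part.

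**1. What the day-1 interval contains.** First dose: day 1 (Table 2 footnote). ECGs on day 1: one just before and one 2 hours after tamoxifen (Cardiac monitoring; Prolonged QTc). Statistic: the maximum in the interval (QT prolongation). The day-1 entry in the tamoxifen arm is therefore max(pre-dose, post-dose). The next interval is days 2-3. A rise above 500 ms at 2 hours that had settled by day 2, for example after the electrolyte correction and dose omission that the Prolonged QTc section prescribes, would be counted under baseline only. A rise that persisted would also be caught in days 2-3.

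**2. How large a first-dose effect might be if QTc tracks concentration.** The Pharmacology and dosing section gives a half-life of 5 to 7 days. With once-daily dosing and r = 0.5^(1/half-life), the first-dose peak as a fraction of the day-14 peak is (1 − r)/(1 − r^14):

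- 5 days: r = 0.871, giving 0.129/0.856 = 15.1%
- 6 days: r = 0.891, giving 0.109/0.802 = 13.6%
- 7 days: r = 0.906, giving 0.094/0.750 = 12.6%

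On accumulation alone, about 13% to 15% of the eventual effect would already be in the day-1 post-dose ECG.

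**3. Consequence for the change regression, if the day-1 maximum were its baseline.** Simulation of 4,000 trials with 25 patients per arm. Assumed, not from the document: between-patient SD 20 ms, within-patient SD 12 ms, true tamoxifen effect 30 ms at the day-14 peak, half-life 6 days (mid-range). Simplifications: days 1-14 only, no HIV term, no omitted doses. Maximum change is regressed on arm and baseline. The correct version uses the day-1 pre-dose ECG as baseline and counts the day-1 post-dose ECG as follow-up.

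| Share of effect present after first dose | Pre-dose baseline | Day-1 maximum as baseline | Attenuation |
|---|---|---|---|
| Accumulation only (about 14%) | 22.40 ms | 20.78 ms | 1 − 20.78/22.40 = 7% |
| At least 30% | 22.45 ms | 18.30 ms | 1 − 18.30/22.45 = 18% |
| At least 50% | 22.46 ms | 14.80 ms | 1 − 14.80/22.46 = 34% |

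The reference is about 22.4 ms rather than 30 ms because the outcome is a maximum over many noisy readings: controls have the whole period to produce a high value by chance, while the full drug effect is reached only late. Averaging the two day-1 ECGs does not cure the problem: the estimates are then 20.85, 18.84 and 16.31 ms.

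**The case against.** The strongest reply is that this is one imprecise row label in a secondary safety table. The day-1 row is still tabulated and compared by arm. A QTc above 500 ms also triggers a cardiac adverse event form, and cardiac events reach the data and safety monitoring board within 10 days, so a severe first-dose event would not vanish from the trial record. This stands as a limit on the harm. It does not rescue the table, which is the planned between-arm summary of QTc over time and would still misclassify the reading.

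Several stronger readings are tempting, but the documents do not support them.

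- *The change regression is contaminated.* Its baseline is undefined. The exclusion criteria use a baseline QTc as an eligibility value and a screening ECG exists, so a pre-dose value may be intended, and an analysis plan not shown may say so. The attenuation above is conditional on the other choice.
- *Any day-1 value above 500 ms must be post-dose, since such patients are excluded.* Eligibility may rest on the screening ECG, and a later pre-dose reading can exceed 500 ms through ordinary variation.
- *Control ECGs are taken at different times.* The timing rule refers only to tamoxifen, so controls have no stated anchor, but nothing shows that timing differed. Tamoxifen is given with the morning amphotericin and fluconazole dose, and controls receive those two drugs together.
- *Chance inflation of a maximum over many ECGs biases the comparison.* With equal numbers of readings it affects both arms alike. ECGs triggered by a value above 500 ms cannot raise the category within that interval, and dropping unscheduled ECGs from a safety maximum has its own cost.
- *Absolute change counts shortening as change.* The natural meaning is milliseconds as opposed to percent.
- *CD4 has the same fault.* "CD4 count will be measured in all patients during week 1 and at day 70" does allow a treated baseline, but it is a separate endpoint, the protocol says only that tamoxifen may affect CD4 cells, and the draws cannot be moved now that enrolment has closed.

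**Conclusion.** The point holds for the interval table as written: the first on-treatment ECG is classed as baseline and excluded from every on-treatment interval. This follows from the text alone and needs no assumption. For the change regression it is a risk, because baseline is left open there. If the day-1 maximum were used, the estimated tamoxifen effect would be reduced by about 7% when QTc follows accumulation, and by 18% to 34% when 30% to 50% of the effect appears after the first dose. Those percentages rest on the assumed SDs and the 30 ms effect; the documents give no information on the acute share. The size is therefore modest on the document's own pharmacology and material only with an appreciable first-dose effect. Early fungicidal activity and the sample size are untouched. The correction is worth making because the error leans towards missing harm on the named safety concern and is cheap to remove.

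**What to change.** - Define baseline QTc, for both the interval table and the change regression, as the last ECG before the first study dose (day-1 pre-dose or, failing that, screening).
- Redraw the first on-treatment interval as day 1 post-dose to day 3, and leave the later intervals as they are. Count the day-1 post-dose ECG as follow-up in the change analysis.
- For controls, classify each ECG as pre- or post-dose by its recorded time relative to the fluconazole and amphotericin dose that both arms share. This assumes that clock times can be recovered; the article lists ECG tracings among its source documents but does not state that times are captured. Where a day-1 time is missing, the screening ECG can serve as baseline.

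The cost is a few lines of specification and programming. No new ECGs, visits or patients are needed. The Trial status section says that enrolment has finished and analysis is under way, so the change can still be made, and it should be recorded as a clarification of the planned analysis.

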42^. In this study, to mitigate any risk of prolonged QT, all patients will have meticulous monitoring and correction of electrolyte disturbances including potassium, calcium and magnesium, and twice daily ECG monitoring. The QT interval will be manually determined by measuring the interval in 3 limb and 3 chest leads, and determining the median (machine derived estimates of the QT interval are unreliable)
^43^. The use of manual estimate of the QT has been shown to have similar performance to high resolution holter ECG monitoring
^43^. Management of QTc prolongation will be in line with the recommendations of the American Heart Association
^32^. The QT interval will be corrected (QTc) for rate using the Framingham formula. Where the QTc is found to be >500ms, the status of the patients K, Ca and Mg levels will be reviewed, corrected if necessary, and the ECG repeated before the next dose of Tamoxifen is due. If the QTc remains >500ms, the next due dose of Tamoxifen will be omitted until it is less than 500ms. When the QTc is less than 500ms, Tamoxifen will be restarted.

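### The model comparing post-baseline QTc categories omits baseline QTc, which costs precision on a side effect of particular interest without biasing the comparison

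*Protocol article*

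**What the plan says.** The QT prolongation paragraph in the analysis section defines normal QTc as below 450 ms (men) or 460 ms (women). The upper two categories are "mildly prolonged (≥450ms for males or ≥460 for females but ≤500ms) and prolonged (>500ms". On summary and comparison it states:

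- "The frequency of patients with a maximum QTc in these categories will be summarized for the following time intervals". Five intervals follow: the baseline day itself, then four later windows that end at day 3, day 7, day 14 and the close of follow-up.
- For the test between arms on these categories, the text reads "Comparisons will be with a proportional odds logistic regression model depending on the treatment arm and HIV infection status".
- A second analysis takes the maximum absolute change from baseline during follow-up and compares arms by linear regression, with "adjustment for HIV status and the baseline QTc interval".

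The exclusion criteria remove patients whose baseline QTc is above 500 ms. The Cardiac monitoring section says "ECGs (50mm/sec) will be performed twice daily immediately before and 2 hours after administration of Tamoxifen during the first 14 days", with further ECGs on days 21 and 28. The abstract's discussion lists QT prolongation among the side effects of particular interest.

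**The concern.** The category a patient reaches after baseline depends heavily on where that patient started. Someone who enters at, say, 480 ms is likely to be classed as mildly prolonged in every interval whether or not tamoxifen does anything. If the model ignores the starting value, this between-patient spread goes into the unexplained variation and hides part of any treatment effect.

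The authors evidently regard the baseline value as relevant. They adjust for it in the linear QTc model, and they adjust the CD4 change for baseline CD4. The category model has an explicit covariate list that leaves it out, so this is not a detail the article merely passes over.

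What is at stake is false reassurance. In a safety comparison with 25 patients per arm, an imprecise odds ratio can look like absence of harm when the data could have shown more.

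**Working it through.** **Inputs from the protocol article.** 25 patients per arm, 1:1 allocation, baseline QTc at most 500 ms, category bounds 450/460 and 500 ms. Two ECGs per day give about 2 × 2 = 4 readings in days 2-3, 4 × 2 = 8 in days 4-7 and 7 × 2 = 14 in days 8-14.

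**Inputs assumed.** The document gives no QTc mean, standard deviation or expected shift. Assumed: mean 425-430 ms, between-patient SD 25-30 ms, ECG-to-ECG SD within a patient 10-20 ms, and in some scenarios a patient-specific drift after baseline. For simplicity a single 450 ms bound is used for both sexes. The article states no power for QTc, so there is no figure of its own to reproduce.

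**Step 1: why baseline matters.** With between-patient SD *b*, within-patient SD *w* and drift SD *d*, the correlation between the baseline reading and the patient's later underlying level (treatment effect aside, and ignoring the entry cut-off) is

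r = b² / √[(b² + w²)(b² + d²)]

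- 25/12, no drift: 625 / √(769 × 625) = 0.90
- 25/12, drift 15: 625 / √(769 × 850) = 0.77
- 25/20, no drift: 625 / √(1025 × 625) = 0.78
- 30/15, drift 20: 900 / √(1125 × 1300) = 0.74

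**Step 2: does omission bias the test?** Simulated trials with no treatment effect (mean 425, between-patient SD 25, within-patient SD 10 or 20, maximum of 4 or 14 ECGs, 300 repetitions, Monte Carlo SE up to 2.9 points):

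| Within SD, ECGs | ≥450 ms at baseline | ≥450 ms on maximum, control / tamoxifen | Rejection, no baseline term | Rejection, baseline term |
|---|---|---|---|---|
| 10, 4 | 17% | 29% / 28% | 5.0% | 11.0% |
| 10, 14 | 17% | 37% / 37% | 7.7% | 7.3% |
| 20, 4 | 21% | 43% / 44% | 6.3% | 4.3% |
| 20, 14 | 20% | 62% / 62% | 5.0% | 3.3% |

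The planned model shows no clear inflation (5.0-7.7%). Taking a maximum lifts both arms alike.

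**Step 3: power for a 20 ms shift, same settings, nominal critical value.**

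| Within SD, ECGs | Category model, no baseline | Category model, baseline | Linear model, baseline |
|---|---|---|---|
| 10, 4 | 52% | 93% | 100% |
| 10, 14 | 63% | 97% | 100% |
| 20, 4 | 59% | 74% | 92% |
| 20, 14 | 60% | 83% | 93% |

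The linear model here uses the interval maximum minus baseline, with no drift. It therefore approximates the planned analysis of maximum change over all follow-up and flatters it somewhat.

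**Step 4: remove the test-size artefact.** The baseline-adjusted test sometimes over-rejects, so critical values were recalibrated so that each test rejects 5% with no effect (days 8-14, 14 ECGs, 500 trials per scenario):

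| Mean / between SD / within SD, drift SD | Without baseline | With baseline | Gain |
|---|---|---|---|
| 425/25/12, none | 56% | 89% | 33 points |
| 425/25/12, 15 | 57% | 78% | 21 points |
| 425/25/20, none | 61% | 75% | 14 points |
| 430/30/15, 20 | 44% | 60% | 16 points |

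A separate set of recalibrated simulations gave 41-59% without baseline and 62-89% with it. The gain is therefore not produced by test size. It is largest where r is highest. In a further set of runs, not recalibrated, power without versus with baseline was 60% v 87%, 45% v 66% and 35% v 44% for drift SD 10, 20 and 30 ms.

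**The case against.** The best reply is that the same section already plans a baseline-adjusted analysis. The linear model on maximum change reached 92-100% power for a 20 ms shift in Step 3, so the plan as a whole is far from blind to a tamoxifen effect. This stands and limits the point. It does not remove it: that model yields one contrast over all follow-up, whereas the category models give the interval-by-interval comparison on the clinical scale, and those odds ratios remain imprecise.

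It is also fair that every power figure rests on assumed distributions, that QTc is one of many secondary endpoints in a pilot study, and that an analysis plan not shown could amend the covariate list.

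Several stronger readings are tempting but unsupported:

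- *That omitting baseline QTc biases the comparison.* Allocation is randomised, and Step 2 shows no clear excess of false positives. Chance imbalance at baseline is part of ordinary sampling error.
- *That a top category starting at the entry cut-off is a defect.* Because baseline values above 500 ms are excluded, a later value above 500 ms is a new crossing. Pre-existing long QTc can fill only the mild category, and the day 1 table shows it.
- *That differing ECG counts per interval distort the result.* The maximum rises with the number of readings, but in both arms, and no test across intervals is planned. Reading error is also limited: "The QT interval will be manually determined by measuring the interval in 3 limb and 3 chest leads, and determining the median".
- *That a high reading should be checked against the next ECG.* After a value above 500 ms the protocol withholds tamoxifen and corrects electrolytes, so a lower next reading may reflect management rather than noise.

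**Conclusion.** The point holds as one of precision. The category model leaves out a baseline value that the trial collects and uses in the companion model. At 25 per arm this lowers power for a 20 ms shift from roughly 60-90% to roughly 40-60%, a difference of 14-33 points in the recalibrated scenarios. Those figures depend on the assumed QTc means, SDs, drift and shift. The direction is secure as long as baseline QTc predicts later QTc, while the size is uncertain and falls as drift grows. The planned linear model offsets part of the loss. Neither the validity of the randomised comparison nor the choice of 500 ms as a category bound is in question. The change is worth making because it is nearly free, not because the planned analysis is invalid.

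**What to change.** In the QT prolongation paragraph, add continuous baseline QTc, using the same value as in the linear model, to the proportional odds models for the post-baseline intervals: days 2-3, 4-7, 8-14 and after day 14. Leave day 1 as a descriptive table. A model there would regress a categorised baseline on itself and come close to separation.

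Optionally, cross-tabulate baseline category against maximum post-baseline category by arm, so that new crossings of 450/460 ms can be told apart from values already present at entry.

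The data are already scheduled for collection, and no dosing or monitoring rule is affected. The cost is one more parameter with 50 patients. The baseline-adjusted likelihood-ratio test rejected 3-11% of the time with no effect across the Step 2 scenarios, so a penalised fit may be used where cells are sparse. The article says enrolment has finished and analysis is under way. The change should therefore be dated, and if the arms have already been compared on QTc, the adjusted result should be reported beside the planned one.
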